## Abstract

**Background:**

Enhanced recovery following total knee arthroplasty (TKA) has been advocated to enhance postoperative recovery. Multimodal cocktail periarticular injection (MCPI) use for pain control in TKA has gained wide acceptance. MCPI-containing corticosteroids are believed to be an effective solution owing to their local anti-inflammatory effects and ability to reduce the local stress response postoperatively. However, there is conflicting evidence regarding its benefits. This trial aims to compare MCPI with a high dose of corticosteroid, normal dose of corticosteroid, and non-corticosteroid during TKA, to assess the effectiveness of MCPI containing corticosteroids in postoperative pain relief, functional improvement, rescue analgesia, and side effects and provide evidence that high-dose corticosteroids result in prolonged pain control and better recovery following TKA.

**Methods:**

This is a double-blinded, randomized, placebo-controlled study. A total of 234 patients scheduled for TKA will be recruited. During surgery, before wound closure, 80 ml of the cocktail analgesic will be injected into the muscle and joint capsule for local infiltration analgesia; the participants will be randomly assigned to three groups to receive a high dose of betamethasone MCPI (group H), normal dose of betamethasone MCPI (group N), and non-betamethasone MCPI (group C). The following indices will be recorded and analyzed: the strongest knee pain experienced during 90° flexion at 6 h, 24 h, 48 h, 72 h, 5 days, 14 days, and 30 days after surgery; 1 min walking ability; and circumference around the patella at 2, 5, 14, and 30 days after surgery; Knee Society knee score at 14 days and 30 days after surgery; C-reactive protein and blood sedimentation; blood sugar 2, 5, 14, and 30 days following surgery; rescue analgesic consumption; and adverse events. If any participant withdraws from the trial, an intention-to-treat analysis will be performed.

**Discussion:**

The results of this study will provide clinical evidence on the effectiveness of MCPI-containing corticosteroids in postoperative pain relief, functional improvement, rescue analgesia, and adverse events, as well as provide evidence on the efficacy of high-dose corticosteroids in prolonged pain control and better recovery following TKA.

**Trial registration:**

Chinese Clinical Trial Registry, ChiCTR2000038671. Registered on September 27, 2020.

**Supplementary Information:**

The online version contains supplementary material available at 10.1186/s13063-021-05655-1.

## Administrative information

Note: The numbers in curly brackets in this protocol refer to SPIRIT checklist item numbers. The order of the items has been modified to group similar items (see http://www.equator-network.org/reporting-guidelines/spirit-2013-statement-defining-standard-protocol-items-for-clinical-trials/).

## Introduction

### Background and rationale {6a}

Total knee arthroplasty (TKA) has been reported to be the most effective procedure for pain relief in patients with advanced osteoarthritis. Enhanced recovery following TKA has been advocated as an evidence-based perioperative care protocol to enhance postoperative recovery in several European countries [1–3]. The stress response following TKA is associated with postoperative nausea and vomiting [4], pain [5], fatigue [6], and decreased muscle strength [7]. Thus, decreasing the inflammatory response after surgery is important for TKA-enhanced recovery protocols. The use of multimodal cocktail periarticular injection (MCPI) for pain control following TKA has gained wide acceptance [8–10]. The agents mostly used in MCPI typically include corticosteroids, local anesthetics, opioids, and nonsteroidal anti-inflammatory drugs (NSAIDs) [11]. Corticosteroids are believed to be a key component owing to their local anti-inflammatory effects and their ability to reduce the local stress response to surgery [12]. However, there is conflicting evidence regarding its benefits. Some studies have shown that postoperative pain is improved with corticosteroids [13–16], whereas others have shown no benefit [17, 18]. The role of MCPI-containing corticosteroids in enhancing recovery following TKA remains inconclusive.

### Objectives {7}

We designed a three-arm, randomized controlled trial containing a high or normal dose of MCPI or an MCPI without corticosteroids to assess postoperative pain relief, functional improvement, rescue analgesia, C-reactive protein (CRP), blood sedimentation, blood sugar, and adverse events, thereby evaluating whether high-dose corticosteroid MCPI contributes to prolonged pain control and better recovery.

### Trial design {8}

This is a protocol for a three-arm, randomized, placebo-controlled trial (Fig. 1). It will follow the recommendations and suggestions of the Consolidated Standards of Reporting Trials (CONSORT 2010). The study will be conducted at a 4-week follow-up. Eligible participants will be randomized in a 1:1:1 ratio for enrollment in one of the three groups to receive a high dose of betamethasone MCPI (group H), normal dose of betamethasone MCPI (group N), and non-betamethasone MCPI (group C).

**Fig. 1 Fig1:**
[figure not shown]
Study flowchart

## Methods: Participants, interventions, and outcomes

### Study setting {9}

This trial has been approved by the ethics committee of The Second Affiliated Hospital of Guangzhou University of Chinese Medicine (approval number: ZF2020-031-01). Patients diagnosed with severe knee osteoarthritis (OA) and scheduled for TKA will be recruited from the Department of Orthopedics, Second Affiliated Hospital, Guangzhou University of Chinese Medicine.

### Eligibility criteria {10}

Eligible patients will include those who meet all of the following inclusion criteria and do not have any of the listed exclusion criteria.

### Inclusion criteria

Meeting the diagnostic criteria for OAAmerican Society of Anesthesiologists (ASA) physical statuses I–IIScheduled for unilateral TKA.Patients aged 50–80 years.Willingness to provide written informed consent and to participate in and comply with the study.

### Exclusion criteria

Participants meeting one or more of the following criteria will be excluded:
Serious mental illness, psychological problems, and inability to communicatePatients with cardiovascular disease, diabetes mellitus, and poor perioperative glycemic control (fasting plasma glucose > 8 mmol/L), severe renal dysfunction, severe hepatic dysfunction, history of gastric ulcer, and coagulation disorderCentral and peripheral nervous system problems that would not allow completion of the postoperative rehabilitation schemeAlcohol and drug abuseAllergies to the ingredients of a multimodal cocktailPrevious major knee surgery, reoperation, or trauma to the knee during the study period

### Who will take informed consent? {26a}

All candidates will undergo a standardized interview process by the investigator (RH) and receive detailed information regarding the study and treatment. The purpose, procedures, and potential risks and benefits of the study will also be explained thoroughly to the participants by RH.

### Additional consent provisions for collection and use of participant data and biological specimens {26b}

This is not applicable. We will not apply additional consent provisions for collection. If this trial supports any further analysis not described in this primary plan, researchers will need to re-obtain consent from the participants.

### Interventions

#### Explanation for the choice of comparators {6b}

The use of MCPI to control pain following TKA has gained wide acceptance [8–10]. The agents mostly used in MCPI typically include corticosteroids, local anesthetics, opioids, and nonsteroidal anti-inflammatory drugs (NSAIDs) [11]. Corticosteroids are believed to be a key component owing to their local anti-inflammatory effects and their ability to reduce the local stress response to surgery [12]. However, there is conflicting evidence regarding its benefits regarding MCPI usage. In this study, participants will be randomly assigned to one of the three groups receiving a high dose of betamethasone MCPI, normal dose of betamethasone MCPI, and non-betamethasone MCPI groups.

#### Intervention description {11a}

All the recruited patients will receive general anesthesia. Cefamandole will be administered intravenously 30 min before and after surgery. Low molecular weight heparin for thromboprophylaxis will be administered subcutaneously 8 h postoperatively and then once daily for 2 weeks. Preoperative oral doses of 400 mg celecoxib will be administered from day 1 before surgery. Postoperatively, all the patients will receive 40 mg of parecoxib sodium twice intravenously until postoperative day (POD) 3, followed by oral doses of 200 mg celecoxib every 12 h for 4 weeks. The chief investigator (DG) will perform all the operations. A Depuy Attune PS prosthesis (Attune ®; DePuy Synthes, Warsaw, IN) will be inserted via a standard medial parapatellar approach in all patients.

#### High dose of betamethasone MCPI (group H)

During surgery, before wound closure, 80 ml of cocktail analgesic will be prepared and injected into the muscle and joint capsule for local infiltration analgesia. Group H will contain 21 mg betamethasone (3 ml), 300 mg 0.75% ropivacaine (30 ml), 5 mg morphine (1 ml), 50 mg flurbiprofen axetil (5 ml), 0.4 ml 1:1000 epinephrine, and 40.6 ml saline.

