#### Normal dose of betamethasone MCPI (group N)

During surgery, before wound closure, 80 ml of cocktail analgesic will be prepared and injected into the muscle and joint capsule for local infiltration analgesia. Group N will contain 7 mg betamethasone (1 ml), 300 mg 0.75% ropivacaine (30 ml), 5 mg morphine (1 ml), 50 mg flurbiprofen axetil (5 ml), 0.4 ml 1:1000 epinephrine, and 42.6 ml saline.

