#### Non-betamethasone MCPI (group C)

During surgery, before wound closure, 80 ml of cocktail analgesic will be prepared and injected into the muscle and joint capsule for local infiltration analgesia. Group C will contain 300 mg 0.75% ropivacaine (30 ml), 5 mg morphine (1 ml), 50 mg flurbiprofen axetil (5 ml), 0.4 ml 1:1000 epinephrine, and 43.6 ml saline.

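### The ropivacaine entry in all three cocktail recipes is arithmetically impossible: 30 ml of a 0.75% solution holds 225 mg, not the stated 300 mg

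*Protocol article*

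**What the plan says.** The protocol article, Intervention description {11a}, sets out one recipe per arm. Every recipe is to total 80 ml: "80 ml of cocktail analgesic will be prepared and injected into the muscle and joint capsule".

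- **Group H:** 21 mg betamethasone in 3 ml; ropivacaine given as "300 mg 0.75% ropivacaine (30 ml"; then "5 mg morphine (1 ml), 50 mg flurbiprofen axetil (5 ml), 0.4 ml 1:1000 epinephrine, and 40.6 ml saline".
- **Group N:** "Group N will contain 7 mg betamethasone (1 ml), 300 mg 0.75% ropivacaine (30 ml"; then "5 mg morphine (1 ml), 50 mg flurbiprofen axetil (5 ml), 0.4 ml 1:1000 epinephrine, and 42.6 ml saline".
- **Group C:** "Group C will contain 300 mg 0.75% ropivacaine (30 ml"; then "5 mg morphine (1 ml), 50 mg flurbiprofen axetil (5 ml), 0.4 ml 1:1000 epinephrine, and 43.6 ml saline".

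The ropivacaine entry is identical in the three arms. No other section of the article gives a ropivacaine mass, strength or volume. Under Implementation {16c}, either the independent investigator or an assisting nurse from outside the study may make up the mixture.

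**The concern.** Any two of mass, strength and volume determine the third. Here all three are given, and they conflict. Someone working from the recipe could reach different ropivacaine doses depending on which two figures they rely on.

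Three things are at stake.

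- **Definition of the treatment.** Ropivacaine is the local anaesthetic in every arm and so part of the background against which betamethasone is tested. A reader cannot reproduce the regimen or compare it with other trials.
- **Safety.** The dose of an injected drug is uncertain by 75 mg in the operative text of a trial that has recruited since October 2020 (Recruitment {15}).
- **Precision.** If preparers resolved the conflict differently, background analgesia would vary between patients. That could add noise to the VAS score from 6 h onward and to rescue tramadol use, which is triggered by a VAS threshold. The trial is sized on differences of 0.8 and 0.4 with an SD of 1.5 (Sample size {14}).

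**Working it through.** **Inputs** (all from the three recipes under {11a}): ropivacaine 300 mg, 0.75%, 30 ml; total 80 ml; the other component volumes as listed. One convention is assumed: the percentage is weight per volume, so 0.75% = 0.75 g per 100 ml = 7.5 mg/ml.

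**1. Attempt to reproduce the stated mass.** Mass = strength × volume = 7.5 mg/ml × 30 ml = 225 mg. The stated 300 mg is not reproduced. The gap is 300 − 225 = 75 mg, and 300/225 = 1.33, so the stated mass is 33% above what the stated strength and volume contain.

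**2. Hold two figures and solve for the third.**

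| Figures kept | Third figure implied | Figure stated |
|---|---|---|
| 0.75% and 30 ml | 7.5 × 30 = 225 mg | 300 mg |
| 300 mg and 0.75% | 300 / 7.5 = 40 ml | 30 ml |
| 300 mg and 30 ml | 300 / 30 = 10 mg/ml = 1.0% | 0.75% |

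**3. Check the volumes against the 80 ml total.**

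| Arm | Sum with 30 ml ropivacaine | Sum with 40 ml, other volumes unchanged |
|---|---|---|
| H | 3 + 30 + 1 + 5 + 0.4 + 40.6 = 80.0 ml | 90.0 ml |
| N | 1 + 30 + 1 + 5 + 0.4 + 42.6 = 80.0 ml | 90.0 ml |
| C | 30 + 1 + 5 + 0.4 + 43.6 = 80.0 ml | 90.0 ml |

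The 30 ml figure agrees with the saline volumes and with the total in every arm. A 40 ml volume would exceed the total by 10 ml (10/80 = 12.5%) unless saline were also changed. With 30 ml kept, the conflict lies between mass and strength, and the volume check cannot decide between them, because both readings fit 80 ml.

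**4. Effect on the injected mixture.** In 80 ml, the final ropivacaine concentration is 225/80 = 2.81 mg/ml or 300/80 = 3.75 mg/ml.

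**5. Is the same fault present elsewhere?** The betamethasone entries agree with each other: 21 mg / 3 ml = 7 mg/ml in group H and 7 mg / 1 ml = 7 mg/ml in group N. The fault found is confined to ropivacaine.

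**The case against.** The strongest reply accepts the arithmetic and disputes its consequences.

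- **The three figures are not equally doubtful.** The 30 ml volume is supported by the saline figure and the total in each recipe, so a preparer would probably follow the volume, and the likely result is one misprinted number applied uniformly. This stands as far as it goes: 40 ml is the reading that fits the text least. But the dose still depends on whether the mass or the strength is misstated, so it remains undetermined.
- **The comparison between arms is not biased.** This stands. The entry is the same in H, N and C, and nothing in the article suggests that preparation would vary by arm.
- **Variation between preparers is conjecture, and its effect on VAS is unquantified.** This also stands. The article allows two possible preparers but does not show that they worked differently. It gives no dose-response figure for ropivacaine, and its sample size rests on pain scores at postoperative day 3 rather than the earliest ones. Added noise is a possibility, not a demonstrated effect.

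Two other defences fail. The entry is unlikely to be a text-extraction fault, since it appears identically in three places. Nor is it detail that an article may leave to a fuller document, since the figures are stated and they conflict.

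**Conclusion.** The concern holds, and the entry must be corrected. As written, the ropivacaine dose in every arm is either 225 mg (from strength and volume) or 300 mg (from the stated mass), a difference of 75 mg or one third of the lower figure. The only assumption is the weight-per-volume reading of the percentage.

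The case rests on a contradictory dose in the operative recipe of all three arms, with its consequences for reproducibility and safety. It does not rest on bias in the betamethasone contrasts, for which there is no evidence, nor on a measured loss of precision in the primary outcome. Which of the figures is wrong cannot be settled from the article, and this review does not say.

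**What to change.** 1. Reconcile the ropivacaine mass, strength and volume, and the saline top-up, in the recipes for groups H, N and C, so that they agree with each other and with the 80 ml total.
2. Compare the pharmacy or operating-room preparation sheet, and the preparation records, with what has been given since recruitment began. Establish whether every patient received the same ropivacaine dose.
3. Issue the corrected recipe as a protocol amendment through the channels in section {25}.
4. Report the dose actually given in the results paper, including any variation between patients.

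If the records show uniform preparation that followed an unambiguous working sheet, the cost is a one-line correction in three places plus the record check, with no change to patients or procedures. If they show that preparation varied, the dose given will have to be documented patient by patient, and the effect on the analysis considered before unblinding.

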#### Normal dose of betamethasone MCPI (group N)

During surgery, before wound closure, 80 ml of cocktail analgesic will be prepared and injected into the muscle and joint capsule for local infiltration analgesia. Group N will contain 7 mg betamethasone (1 ml), 300 mg 0.75% ropivacaine (30 ml), 5 mg morphine (1 ml), 50 mg flurbiprofen axetil (5 ml), 0.4 ml 1:1000 epinephrine, and 42.6 ml saline.

#### Non-betamethasone MCPI (group C)

During surgery, before wound closure, 80 ml of cocktail analgesic will be prepared and injected into the muscle and joint capsule for local infiltration analgesia. Group C will contain 300 mg 0.75% ropivacaine (30 ml), 5 mg morphine (1 ml), 50 mg flurbiprofen axetil (5 ml), 0.4 ml 1:1000 epinephrine, and 43.6 ml saline.

#### Criteria for discontinuing or modifying allocated interventions {11b}

Participants are permitted to withdraw from the study at any time without consequence. When serious adverse events are reported during the trial, either participant is able to make a withdrawal request or the chief investigator can consider to cease the trial for the participant.

#### Strategies to improve adherence to interventions {11c}

The following measures will be taken to improve adherence to the interventions and follow-up.
All participants will be informed of the intervention routine, potential benefits, and risks to fully understand the significance of their involvement in the study.3MCPI is a routine strategy for TKA pain control whether the patient is “in” or “out ” of the trial. As the intervention will be a one-off event, once consent is obtained, the MCPI formula according to allocation will be executed.

#### Relevant concomitant care permitted or prohibited during the trial {11d}

After surgery, tramadol hydrochloride injections or sustained-release tablets will be applied for rescue analgesia if the patient experiences a knee pain visual analog scale (VAS) score ≥ 4 cm. The participants’ usage of rescue analgesics will be recorded throughout the study. No other opiate analgesia will be permitted during the trial.

#### Provisions for post-trial care {30}

As a routine follow-up plan, participants are advised for clinic follow-up visits at 2 weeks, 4 weeks, 8 weeks, and 3 months; the investigators (CZ and LZ) will contact the participants for routine clinical follow-up as post-trial care. Previous studies on the intravenous use of corticosteroids have shown that postoperative blood glucose rise, gastrointestinal ulcers, and poor wound healing could occur. In this study, the topical use of corticosteroids may have similar risks during the trial. These adverse events are included in the common adverse events of TKA and will be covered by the government health care insurance.

### Outcomes {12}

#### Primary outcome measures

The primary outcome will be knee pain during 90° flexion via VAS pain score measured by a 10-cm horizontal line scale [19]. The patients will be asked, “How much pain do you have this moment?”, the patient will then mark on the 10-cm horizontal line VAS. Zero means “absence of pain,” while 10 represents “the worst pain” VAS has been proven to be a valid and reliable outcome measure for recording pain with ICC = 0.96 to 0.98, according to a previous study [20]. The VAS score will be evaluated at preoperative day 1; postoperative 6, 24, 48, and 72 h; day 5; day 14; and day 30 following the surgery.

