#### Sample size {14}

The calculation of the sample size was based on previous studies. Ikeuchi et al. [13] reported that the POD 3 VAS scores were 27 ± 16 mm in the steroid group and 43 ± 18 mm in the control group. Kwon et al. [4] reported that POD 3 VAS scores were 35 mm in the steroid group and 41 mm in the control group. We assumed that the mean difference in the VAS score between the high-dose betamethasone group and control group was 0.8, and the mean difference between the normal-dose betamethasone group and control group was 0.4. An estimated standard deviation (SD) of 1.5, significance level (*α*) of 0.05, and power of test (*β*) of 0.8000 will be adopted. Based on the former data, the sample size was calculated as 69 participants per group. Assuming a dropout rate of 10%, the final sample size will be 78 participants per group, and 234 participants will be required for the three groups.

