### Statistical methods

#### Statistical methods for primary and secondary outcomes {20a}

Perioperative outcomes will be summarized using the mean ± SD for continuous variables and the ratio for categorical variables. All statistical analyses will be conducted using the SPSS software (version 13.0. for Windows; SPSS, Inc., Chicago, USA). For continuous variables, the Kolmogorov–Smirnov test will be used to detect the normality of distribution. Analysis of variance (ANOVA) will be used to compare the differences among the three groups, and Dunnett’s *t* test will be conducted to compare the between-group differences. For categorical variables, the chi-square test will be conducted to compare the intragroup differences, and partitions of chi-square methods will be used to compare the between-group differences.

For repeatedly measured outcomes, multivariate analysis for repeated measures ANOVA test will be performed to compare the difference between the three groups, which contains the three intervention groups, time, and group-time interaction. Dunnett’s test will be applied for post hoc comparisons. When the group-time interaction showed a significant difference, a one-way repeated measures ANOVA was conducted to identify the difference in effect between the three intervention groups. The significance level will be set at *α*=0.05. Statistical analyses will be performed by an independent investigator.

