## Discussion

In TKA, an enhanced recovery strategy warrants improved patient comfort during hospital stay and accelerated discharge. Consequently, measures to control pain and accelerate rehabilitation are important. Although the MCPI technique has been proven to be a safe and cost-effective measure, the gold standard for drug combinations has not yet been established. Corticosteroid addition to MCPI is believed to be a key component owing to its local anti-inflammatory effects and ability to reduce the local stress response following surgery. However, there is conflicting evidence regarding its benefits for pain control following TKA. Christensen et al. [18] conducted a randomized controlled trial that compared patients who had MCPI with 40 mg of methylprednisolone or without corticosteroids, and the only significant result was a decreased LOS in the steroid cohort (2.6 vs. 3.5 days). There was no difference in pain scores, ROM, or Knee Society scores at any time point. Chia et al. [17] compared patients who had an MCPI containing high- or low-dose corticosteroid with patients’ MCPI without corticosteroid, and they were unable to find any significant clinical effect on postoperative ROM advantage and pain relief at the two different dosages. In contrast, Seah et al. [16], who used 40 mg of triamcinolone acetate, found a significant reduction in the early postoperative pain scores and lasting increase in the ROM in the steroid group. Wang et al. [10] found that addition of corticosteroids to an analgesic cocktail could prolong the analgesic effects of local anesthetics, reduce inflammation, slightly improve immediate postoperative pain relief, and accelerate recovery in the first 24 h following TKA. They concluded that the additional analgesic effects of corticosteroids were mild and transient, and prospective studies are still needed to determine the best cocktail of periarticular infiltration analgesia. A meta-analysis by Chai et al. [29] demonstrated that cocktail analgesia containing corticosteroid periarticular injection did not contribute to pain relief within 12 h postoperatively; however, from 24 to 72 h, it significantly decreased the pain score at rest and reduced total rescue opioids. A recent meta-analysis by Li et al. [30] demonstrated that adding corticosteroids to multimodal cocktail periarticular injection can relieve the POD 1, POD 2, and POD 3 pain intensity at rest following TKA, with no significant difference in the VAS score at the operation night, POD 4, POD 5, POD 7, and 2 weeks following the operation. Owing to these conflicting results, we plan to design a three-arm, double-blinded randomized controlled trial containing a high or normal dose of corticosteroid MCPI and a noncorticosteroid MCPI to assess their effectiveness in postoperative pain relief, functional improvement, rescue analgesia, and side effects. This study will also provide clinical evidence on the effect of high-dose corticosteroid adjuvant to MCPI on prolonged pain control and better recovery following TKA.

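### No primary time point or deciding effect is named for flexion VAS, and the 69 per group comes from a single-time ANOVA, so the stated 80% power is not that of the planned repeated-measures analysis and the type I error is not fixed

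*Protocol article*

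**What the plan says.** Four places in the protocol article bear on this.

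- **Primary outcome measures (Outcomes {12}).** The outcome is defined without a time: "The primary outcome will be knee pain during 90° flexion via VAS pain score measured by a 10-cm horizontal line scale". The schedule has one preoperative and seven postoperative assessments: "The VAS score will be evaluated at preoperative day 1; postoperative 6, 24, 48, and 72 h; day 5; day 14; and day 30". No time, average or other summary is singled out.
- **Sample size {14}.** Both cited sources are POD 3 results. One "reported that the POD 3 VAS scores were 27 ± 16 mm in the steroid group and 43 ± 18 mm in the control group"; the other "reported that POD 3 VAS scores were 35 mm in the steroid group and 41 mm in the control group". The section then assumes differences from control of 0.8 (high dose) and 0.4 (normal dose), SD 1.5, alpha 0.05 and power 0.80. It arrives at 69 per group, or 78 after dropout. The assumed differences and SD carry no time label of their own.
- **Statistical methods for primary and secondary outcomes {20a}.** For repeated outcomes, "multivariate analysis for repeated measures ANOVA test will be performed to compare the difference between the three groups", with terms for group, time and their interaction. Dunnett's test is used post hoc, and a further ANOVA follows a significant interaction. Alpha is 0.05 throughout. No term is designated as the one that answers the primary question.
- **Objectives {7}.** The trial is to show whether the high dose gives longer-lasting pain control and better recovery.

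**The concern.** The primary outcome, the sample size and the analysis are all stated, but they do not describe the same test. The sample size is for one comparison of three means at one time. The analysis is a model over several times with at least two terms on which a treatment difference could be claimed.

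Two consequences follow. First, the stated 80% power belongs to a test that the plan does not designate as primary. The power of the planned model depends on which term is read and on how long the effect lasts. Second, the trial could be called positive on the group effect, on the interaction or on a follow-up comparison, and no rule limits which. Dunnett's adjustment covers the comparisons of two doses with control; it does not cover seven times. A claim of lasting benefit is the one most exposed, because it could come to rest on a single late time chosen after the results are known.

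**Working it through.** **Inputs from the article.** Differences 0 / 0.4 / 0.8 cm (control, normal dose, high dose), SD 1.5, alpha 0.05, 69 per group before dropout, seven postoperative times.

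**Assumed, because the article does not give it.** A common correlation ρ between VAS at any two times, varied from 0.3 to 0.9, with the same SD at each time.

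**1. The plan's own figure.** For a one-way ANOVA on three groups, the noncentrality is λ = n Σ(μᵢ − μ̄)² / SD². Here μ̄ = 0.4 and Σ(μᵢ − μ̄)² = 0.16 + 0 + 0.16 = 0.32.
- n = 69: λ = 69 × 0.32 / 2.25 = 9.81 on 2 and 204 degrees of freedom, power 0.8015.
- n = 68: λ = 9.67, power 0.795.

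The smallest n with at least 80% power is therefore 69, an exact match. The arithmetic is right, and it is for one time point.

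**2. Power of the repeated-measures group effect.** This term compares patients' means over the seven times. The SD of such a mean is 1.5 × √((1 + 6ρ)/7). If the effect is present at only three of the seven times, the mean differences shrink to 0.8 × 3/7 = 0.343 and 0.4 × 3/7 = 0.171.

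| ρ | SD of 7-time mean | Power, effect at all 7 times | Power, effect at 3 of 7 times |
|---|---|---|---|
| 0.3 | 0.949 | 0.996 | 0.455 |
| 0.5 | 1.134 | 0.966 | 0.332 |
| 0.7 | 1.293 | 0.908 | 0.263 |
| 0.9 | 1.434 | 0.838 | 0.220 |

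**3. Power of the interaction in the three-of-seven case.** Take the effect to be present at 24, 48 and 72 h only. After removing group and time means, the sum of squared interaction terms is 0.32 × (3 − 9/7) = 0.5486. Then λ = 69 × 0.5486 / (2.25 × (1 − ρ)) on 12 and 1224 degrees of freedom.
- ρ = 0.3: λ = 24.0, power 0.93.
- ρ = 0.5: λ = 33.6, power 0.99.
- ρ = 0.7 and above: power over 0.99.

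The multivariate (Wilks) version, by simulation, gives 0.91, 0.99 and about 1.00 at ρ = 0.3, 0.5 and 0.7.

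**4. Type I error under each possible decision rule.**
- Group effect alone decides: 0.05.
- Either the group effect or the interaction counts, treating the two tests as independent: 1 − 0.95² = 0.0975.
- A difference at any one of seven times counts, each tested at 0.05 with no gate: 1 − 0.95⁷ = 0.30 if the times were independent. By simulation under no effect (69 per group, common correlation) the rate is about 0.27, 0.23, 0.18 and 0.12 at ρ = 0.3, 0.5, 0.7 and 0.9. Separate runs at ρ = 0.3 ranged from 0.267 to 0.280.

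**The case against.** The strongest reply is that the plan does contain a global analysis. The repeated-measures model is fitted once, the extra ANOVA follows only a significant interaction, and Dunnett's test is post hoc. Nothing says that VAS will be tested separately at each time at 0.05. A sustained effect would be found by the group term and a brief one by the interaction, so the model as a whole has good power either way. One may add that a condensed article can leave the choice of deciding term to an SAP.

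Much of this stands, and it rules out three stronger readings that a reader might infer.

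- *That the trial has several times the nominal error.* The 0.12 to 0.27 range needs ungated testing at each time, which {20a} does not state. If the group effect alone decided, alpha would be 0.05.
- *That the trial loses most of its power.* That is true only of the group effect under a short-lived benefit. In that same case the interaction has over 90% power, and with a constant effect the group term exceeds the planned 80%.
- *That the protocol itself expects benefit only on POD 1 to 3.* The Discussion does report a meta-analysis with "no significant difference in the VAS score at the operation night, POD 4, POD 5, POD 7, and 2 weeks following the operation". But that concerns pain at rest, not in flexion, and it is cited among conflicting results. The stated aim is longer-lasting control.

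What does not stand is the appeal to an SAP. The article itself fixes the outcome, the sample size and the analysis, and the three do not match. Good power on one term or the other also does not settle which term answers the question. In the three-of-seven case the two would often disagree, and letting either count doubles the error rate.

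**Conclusion.** The point holds as a mismatch and an unfixed decision rule. The sample-size arithmetic is correct for a single-time three-group ANOVA, but the 80% does not carry over to the repeated-measures analysis. There, group-effect power runs from 0.22 to 0.996, depending on how long the effect lasts and on the correlation between times. Type I error is not shown to be wrong; it is undetermined, at 0.05 or about 0.10 under the two readings closest to the text and higher only under per-time testing.

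The ranges rest on the assumed correlations of 0.3 to 0.9, equal SDs over time, and an effect of 0.8/0.4 cm wherever it is present. The absence of a primary time and of a deciding term rests on no assumption.

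**What to change.** Before unblinding, name one deciding test at alpha 0.05 in the protocol and the registry. Either of two choices is sound.

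- **Flexion VAS at 72 h**, compared once across the three groups. This is the POD 3 time of the cited data and keeps 69 per group and 80% power.
- **One prespecified repeated-measures contrast**, for example the group effect averaged over a stated set of times. This stays closer to the planned model and to the aim of lasting relief, but its power must be restated with an explicit correlation and effect pattern.

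Make the remaining times and model terms secondary, in a fixed order or with Holm adjustment. Keeping all seven times as co-equal primaries is the expensive route: at 0.05/7 each, power at one time with 69 per group falls to 0.545, and 106 per group would be needed for 80%.

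The recommended change costs wording only and needs no further patients if 72 h is chosen. The drawback is that a difference seen only at another time becomes a secondary result. If 72 h is primary, that includes a late benefit, which is what the objective is about, so the investigators should weigh this when choosing between the two options.
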